##### Systolic function variables

LV ejection fraction (LVEF), obtained by the Simpson biplane methodPercentage of variation in ventricular diameter (%∆D) = [LVDD − LVSD)/LVDD] × 100Maximum systolic excursion velocity of the mitral annulus: S wave, obtained by spectral recording of the movement of mitral annulus, in its medial and lateral portions on tissue Doppler

##### Diastolic function variables

LAV (mL), normalized to the body surface (LAVI, mL/m^2^)Maximum early ventricular filling velocity (E wave peak, cm/s): obtained by spectral Doppler recording of the transmitral diastolic flowMaximum late filling velocity during atrial contraction (A wave peak, cm/s): obtained by spectral Doppler recording of the transmitral diastolic flowE/A ratioIsovolumetric relaxation time of the LV (ms), corresponding to the period between the end of the ventricular ejection and the beginning of mitral transvalvular diastolic flowE-wave deceleration time (ms) corresponding to the time between the initial velocity peak of the mitral transvalvular flow and its extrapolation to the baselineMaximum excursion velocities of the mitral annulus, in the early ventricular filling phase (E’ medium, cm/s) and during the atrial contraction (A’ medium, cm /s), obtained by the spectral recording of tissue Doppler of movement of the ring mitral, in its medial and lateral portionsE/E’ medium ratio

### Laboratory evaluation

A)Fasting plasma glucose test: to evaluate glycemic control. It reflects the lowest plasma glucose values of the day. Possible to establish comorbidities such as type 2 DM [42]B)Glycosylated hemoglobin: allows the monitoring of glycemic control in diabetic patients since it provides information without large fluctuations on the retrospective index of plasma glucose and is directly related to the risk of complications in patients with type 1 and 2 DM [43]C)High density lipoproteins and low density lipoproteinsD)Pro-inflammatory cytokines: evaluate levels of inflammatory response in the body, interleukins (IL-1β, IL-10, and IL-6), C-reactive protein, and tumor necrosis factors [44]

### Quality of life assessment

#### EuroQol

The European (5D) Quality of Life Scale (EuroQol) will be used to assess the impact of stroke on an individual’s quality of life through five parameters structured on mobility, personal care, usual activities, pain/discomfort, and anxiety/depression ranging from 0 to 10. The higher the score, the worse the perception of quality of life. At the end of the test, the patient should report their health on an ordinal scale of 0 to 100, and the closer to 0, the worse their condition, and the closer to 100, the better [45, 46].

## Sample size estimation

The sample size was calculated to match primary outcome with sample size estimation.

According to Framingham data [47], an increase of 20 g/m^2.7^ in left ventricular mass index presents a hazard ratio to hard end points of about 1.5; in this study the standard deviation was 30 g/m^2.7^. To detect these clinically significant differences between groups, with a fixed alpha error of 0.05 and beta error of 0.20, 37 patients per group will be needed.

According to the cohort of Presher et al. [48], an increase of 66 m in the 6-min walking test discriminates survivors from non- survivors among heart failure patients; in that study the standard deviation was 90 m. To detect these clinically significant differences between groups, with a fixed alpha error of 0.05 and beta error of 0.20, 31 patients per group will be needed.

Therefore, we will study 40 patients per group to detect these differences properly.

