**Methods/design:**

This is a randomized controlled trial including patients with ischemic stroke in the chronic phase. The patients will be evaluated at the beginning of the study and after 16 weeks. This will include clinical and physical evaluation, 6-min walk test, neurological assessment, nutritional assessment, ambulatory blood pressure monitoring, transthoracic echocardiography, and assessment of the quality of life. The sample size has been determined as 40 patients, who will be divided into two groups: control group (CG; *n* = 20) and intervention group (IG; n = 20). The CG will undergo conventional physiotherapy for 45 min, three times a week, up to 16 weeks, while the IG will be put on a cardiovascular rehabilitation program consisting of heating, aerobic exercise, and muscle strengthening for 45 min, three times a week, for 16 weeks. The primary endpoint will be functional capacity following a 6-min walk test (delta maxVO_2_) and morphofunctional echocardiographic variables (indexed left ventricular mass) before and after the intervention.

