## Methods/design

### Design

This single-center, randomized, single-blind, parallel group study of 40 patients with stroke will be conducted in accordance with the Consolidated Standards of Reporting Trials (CONSORT) 2010. A flow diagram of the study is presented in Fig. 1.

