### Patient population

Participants were recruited from the Cardiac RemOdeliNg and functional capacity in patients with Stroke (CRONuS) trial, a single-center, randomized, single-blinded study of cardiac rehabilitation in 40 individuals with stroke at UNESP – University Estadual Paulista, Botucatu Medical School, Brazil.

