## Procedures (template)

Individuals diagnosed with ischemic stroke will be sent to the rehabilitation center after discharge from the hospital. All individuals with ischemic stroke confirmed by a computed tomography (CT) or magnetic resonance imaging (MRI) scan will be invited to participate in the study. The patient, a family member, or guardian must sign an informed consent form. The individuals will then be evaluated for their clinical and neurological status. Individuals will be assessed using the National Institutes of Health Stroke Scale (NIHSS), the Barthel Index of ADL, and the mRS. The aerobic capacity will be evaluated by VO_2max_, functional capacity will be assessed by a 6-min walk test, nutritional status by electric bioimpedance, cardiologic examination by ecocardiography, and laboratory exams and the quality of life will be based on the European Quality of Life Scale. The tests will be performed by an investigator who is blinded to the treatment that the patient received before the first session and a week after the last session. After the clinical screening, they will be randomized into the following two groups: 1) control group (CG; 20 patients); 2) intervention group (IG; 20 patients) (Fig. 2).

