## Statistical analysis

Continuous variables will be expressed as means and standard deviations or medians and interquartile ranges. The associations between clinical and echocardiographic variables will be evaluated by Student’s *t*-test for the variables with normal distribution, or Mann-Whitney test with non-normal distribution for comparison between groups. Comparisons between the values before and after the intervention will be made using the paired *t*-test. The associations between the continuous variables, in the same group and before and after the intervention, will be evaluated by means of repeated measures ANOVA correlation test. Data will be analyzed using SPSS version 22 (SPSS Inc., Chicago, IL, USA) and will be considered statistically significant at a *p* value < 0.05.

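### The sample-size section plans 40 patients per group, but the rest of the protocol describes 40 patients in total (20 per group); one size must be stated, with the power that belongs to it

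*Protocol article*

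**What the plan says.** All references are to the protocol article.

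- **Sample size estimation.** For left ventricular mass index, with a difference of 20 g/m^2.7 and an SD of 30: "with a fixed alpha error of 0.05 and beta error of 0.20, 37 patients per group will be needed". For the 6-minute walk, with a difference of 66 m and an SD of 90 m: "with a fixed alpha error of 0.05 and beta error of 0.20, 31 patients per group will be needed". The section then concludes: "Therefore, we will study 40 patients per group to detect these differences properly".
- **Abstract, Methods/design.** "The sample size has been determined as 40 patients, who will be divided into two groups", with 20 given for each group.
- **Design.** "parallel group study of 40 patients with stroke", a total with no split.
- **Patient population.** "single-blinded study of cardiac rehabilitation in 40 individuals with stroke", again a total with no split.
- **Procedures (template).** "1) control group (CG; 20 patients); 2) intervention group (IG; 20 patients".
- **Randomization and blinding.** Allocation is 1:1, so a total of 40 means 20 per group.
- **Statistical analysis.** Groups are compared by t-test or Mann-Whitney test. A result "will be considered statistically significant at a *p* value < 0.05"; sidedness is not stated.

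**The concern.** The planned size differs by a factor of two between the section that justifies it and the four places that describe the trial. These are positive statements that cannot all be true, so this is not a detail left to a fuller document.

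A reader cannot tell whether recruitment is complete at 40 patients or at 80. If it is 40, the trial falls short of both requirements that its own sample-size section sets, and no power is stated for the design being run. If it is 80, enrolment beyond 40 will look like an unexplained expansion against four passages.

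**Working it through.** **Inputs**, all from Sample size estimation unless noted:
- Mass index: difference 20 g/m^2.7, SD 30, so d = 20/30 = 0.667.
- Walk distance: difference 66 m, SD 90 m, so d = 66/90 = 0.733.
- Alpha 0.05, beta 0.20; 1:1 allocation (Randomization and blinding).
- Sidedness: not stated; inferred in step 1.

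**Step 1: reproduce the plan's own figures.** The normal approximation is n per group = 2(1.960 + 0.842)² / d².
- Mass index: 15.70 / 0.444 = 35.3, rounded up to 36.
- Walk distance: 15.70 / 0.538 = 29.2, rounded up to 30.

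Solving with the noncentral t distribution instead gives 36.3 and 30.2, rounded up to 37 and 31. Both match the document exactly. A one-sided test would need only 29 and 24 per group, so the plan's figures are two-sided and they are per group.

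**Step 2: power at each candidate size.** The noncentrality parameter is d × √(n/2), with 2n − 2 degrees of freedom and two-sided alpha 0.05.

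| Per group | Outcome | Noncentrality | Critical t | Power |
|---|---|---|---|---|
| 20 | Mass index | 0.667 × √10 = 2.108 | 2.024 | 53.8% |
| 20 | Walk distance | 0.733 × √10 = 2.319 | 2.024 | 61.8% |
| 40 | Mass index | 0.667 × √20 = 2.981 | 1.991 | 83.8% |
| 40 | Walk distance | 0.733 × √20 = 3.280 | 1.991 | 90.0% |

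At 20 per group, beta is therefore 0.46 and 0.38. The normal approximation gives similar power at 20 per group: 55.9% and 64.0%.

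**Step 3: difference detectable with 80% power at 20 per group.** Solving for d gives 0.909.
- Mass index: 0.909 × 30 = 27.3 g/m^2.7, against the planned 20.
- Walk distance: 0.909 × 90 = 81.8 m, against the planned 66.

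**Step 4: sensitivity to sidedness.** Even with a one-sided 0.05 test, 20 per group gives 66.5% and 73.6%, still below 80%.

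**The case against.** A reader might infer more than the document supports, in four ways.

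1. *That the stated beta of 0.20 is false.* It is not. The section attaches it to 37 and 31 per group, where it is correct, and no passage claims 80% power for 20 + 20. The arithmetic stands; only the concluding sentence conflicts with the other places.

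2. *That the trial is underpowered.* This holds only if 20 + 20 is the real design. The sample-size section is the only one that derives a size, so 40 per group may well be the intention, and then the power criticism falls away. The greater number of places giving 40 in total does not settle it, and the document does not show how the discrepancy arose.

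3. *That 54% and 62% are the power of the final analysis.* They are the power under the section's own inputs and a two-group t-test. If the SDs of 30 and 90 describe single measurements, an analysis using baseline could do better. Reaching 80% with 20 per group would then need a baseline-to-follow-up correlation of about 0.68 (mass index) and 0.59 (walk) with baseline adjustment, or about 0.73 and 0.67 with change scores. But the document gives no correlation, does not say what kind of SDs these are, and plans no baseline-adjusted comparison. This route therefore neither rescues 20 per group nor belongs in the correction.

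4. *That 62% is the power for a primary endpoint.* The calculation is for walk distance in metres. The Abstract and Primary outcome measures write the endpoint as a change in maximal oxygen uptake following the walk test, so the figure needs that label.

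What stands after all four is the contradiction itself, together with the conditional power figures.

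**Conclusion.** The point holds as an internal contradiction that has to be resolved: 40 per group in one section, 40 in total or 20 per group in four others, with nothing to reconcile them. The document does not settle which is intended.

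If 20 per group is the trial being run, the requirement of 37 and 31 per group is not met, and power is about 54% and 62% instead of 80%. If 40 per group is being run, it is met, with power of about 84% and 90%.

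These figures rest on the document's own differences and SDs, a two-sided t-test at 0.05 (inferred from the exact reproduction of 37 and 31) and no loss of patients. Any loss would lower them.

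**What to change.** State one size in the Abstract, Design, Patient population, Procedures and Sample size estimation.

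- **If 20 per group is the trial being run:** replace the concluding sentence of Sample size estimation with the actual size. State that, on that section's inputs, power is about 54% for 20 g/m^2.7 in mass index and about 62% for 66 m in walk distance, and that 80% power is reached only for about 27 g/m^2.7 and 82 m. The sentences giving 37 and 31 per group are correct and can stay, as the requirement that is not met.
- **If 40 per group is the trial being run:** correct the other four places to 80 patients, 40 per group, with power of about 84% and 90%.

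In either case, label the walk figures as power for walk distance.

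The cost is a wording correction or a short amendment; restating the size that is being run enrols nobody extra. The downside is that the stated power becomes less favourable if 20 per group stands.

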## Statistical analysis

Continuous variables will be expressed as means and standard deviations or medians and interquartile ranges. The associations between clinical and echocardiographic variables will be evaluated by Student’s *t*-test for the variables with normal distribution, or Mann-Whitney test with non-normal distribution for comparison between groups. Comparisons between the values before and after the intervention will be made using the paired *t*-test. The associations between the continuous variables, in the same group and before and after the intervention, will be evaluated by means of repeated measures ANOVA correlation test. Data will be analyzed using SPSS version 22 (SPSS Inc., Chicago, IL, USA) and will be considered statistically significant at a *p* value < 0.05.

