**Discussion:**

We expect to observe an improvement in cardiac structural and functional abnormalities in the IG, on echocardiography and biochemical examination, and that the improvement of these parameters after cardiovascular rehabilitation will have a favorable impact on the functional capacity and quality of life of patients after stroke.

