### Primary outcome measures

The primary endpoint will be measured as functional capacity following a 6-min walk test (delta maxVO_2_) and morphofunctional echocardiographic variables (indexed left ventricular mass) before and after the intervention.

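### The before-after values that define both primary endpoints are assigned to a paired t-test; the between-group test is tied to neither endpoint, and no analysis adjusts for baseline

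*Protocol article*

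**What the plan says.** The design is a "randomized, single-blind, parallel group study of 40 patients with stroke". Under Primary outcome measures, the endpoints are the change in maximal oxygen uptake and "morphofunctional echocardiographic variables (indexed left ventricular mass) before and after the intervention".

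The Statistical analysis section names three procedures:

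- **Between groups.** The sentence opens "The associations between clinical and echocardiographic variables will be evaluated by Student"'s t-test and continues "for the variables with normal distribution, or Mann-Whitney test with non-normal distribution for comparison between groups". It names no endpoint, time point or change score.
- **Before against after.** "Comparisons between the values before and after the intervention will be made using the paired" t-test.
- **Repeated measures.** Associations among continuous variables "in the same group and before and after the intervention, will be evaluated by means of repeated measures ANOVA correlation test". No group-by-time term is named.

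No baseline covariate appears anywhere. The Sample size estimation section, by contrast, sizes the trial for differences between the groups. The Data monitoring section schedules the same assessments in both arms at the start and after 16 weeks, so baseline values will be available.

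**The concern.** A paired test compares patients with themselves. It measures change over time, which mixes any treatment effect with whatever would have happened anyway. Under Intervention, both arms receive supervised or outpatient exercise-based therapy three times a week for 16 weeks, so change in both arms is plausible. A paired result in one arm, or a pair of such results set side by side, does not estimate the difference between arms.

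The article assigns the before-after values to that test and leaves the between-group test without a named outcome. Two analysts could therefore follow the same text and report different primary results. Nor does any stated analysis use the baseline value to reduce variance. That matters most if the trial has 20 patients per arm, as the Abstract and Procedures state, rather than the 40 per group in Sample size estimation (a separate discrepancy).

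**Working it through.** **1. Inputs.** From Sample size estimation: left ventricular mass index (LVMI) difference 20, SD 30 g/m^2.7; 6-minute walk distance (6MWD) difference 66 m, SD 90 m; alpha 0.05; power 0.80. The SDs are not stated to be SDs of change. Assumptions not in the article: two-sided alpha, equal variance at both visits, baseline/follow-up correlation r from 0.3 to 0.8, and a common change in both arms of 0 to 1 SD of change.

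**2. The plan's own figures.** Standardised differences are 20/30 = 0.667 and 66/90 = 0.733. A two-sided two-sample t-test at 80% power needs 36.3 and 30.2 per group, rounded up to 37 and 31, exactly as stated. (One-sided alpha gives 28 and 23 by the normal approximation and does not reproduce them.) The sample size therefore assumes an unadjusted between-arm comparison on the raw SD.

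**3. Paired tests read arm by arm, no treatment effect.** If each arm's paired test has power p, the probability of significance in the intervention group (IG) and not in the control group is p(1 − p), which cannot exceed 25% (at p = 0.5).

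| Common change (SD of change) | 20 per arm: p | IG only | 40 per arm: p | IG only |
|---|---|---|---|---|
| 0 | 0.05 | 5% | 0.05 | 5% |
| 0.2 | 0.14 | 12% | 0.23 | 18% |
| 0.3 | 0.25 | 19% | 0.46 | 25% |
| 0.45 | 0.48 | 25% | 0.79 | 16% |
| 0.5 | 0.56 | 25% | 0.87 | 11% |
| 0.7 | 0.84 | 13% | 0.99 | 1% |
| 1.0 | 0.99 | 1% | 1.00 | 0% |

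In simulation, a between-arm t-test of change stayed at about 5% (4.8–5.4%) in every scenario.

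**4. Power of the possible between-arm analyses.** The effective standardised difference is d for follow-up only, d/√(2(1 − r)) for change scores, and d/√(1 − r²) for ANCOVA. Example, LVMI at r = 0.7: change score 0.667/√0.6 = 0.861; ANCOVA 0.667/√0.51 = 0.934. Power by the t distribution, 20 per arm:

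| | r = 0.3 | 0.5 | 0.7 | 0.8 |
|---|---|---|---|---|
| LVMI, follow-up only | 54% | 54% | 54% | 54% |
| LVMI, change score | 41% | 54% | 76% | 90% |
| LVMI, ANCOVA | 58% | 66% | 82% | 93% |
| 6MWD, follow-up only | 62% | 62% | 62% | 62% |
| 6MWD, change score | 48% | 62% | 83% | 95% |
| 6MWD, ANCOVA | 66% | 74% | 89% | 96% |

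At 40 per arm, LVMI power is 84% for follow-up only. At r = 0.5 and 0.7 it is 84% and 97% for change scores, and 93% and 98% for ANCOVA.

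The 6MWD rows use the variable on which the article based its calculation. The article gives no SD for change in oxygen uptake, so the corresponding power for that endpoint cannot be computed.

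**The case against.** A reader might infer that the plan contains no valid test of the randomised effect. The article does not support that. It names a "Mann-Whitney test with non-normal distribution for comparison between groups" with Student's t-test as the alternative, the trial is sized for differences between groups, and one endpoint is already a change score. A t-test of change between arms, or an unadjusted follow-up comparison, would be valid under randomisation. The wording about associations makes the sentence unclear; it does not remove the test.

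A reader might also infer that benefit will be claimed when the paired test is significant in the intervention arm and not in the control arm. No passage says so. The Abstract's "We expect to observe an improvement in cardiac structural and functional abnormalities in the IG" is an expectation, not a decision rule.

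The sizes also have limits. The 25% is a ceiling, and the rate falls to about 1% or below when the common change is large. The ANCOVA gain depends on the comparator: at 20 per arm it is about 12 points over a change-score test at r = 0.5, but only about 2–6 points at r = 0.7–0.8. Over follow-up only, it is about 4 points at r = 0.3.

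Finally, covariate adjustment is often left to an analysis plan, and one may exist. That excuses the missing covariate, taken alone. It does not excuse assigning the values that define the primary endpoints to a within-patient test while leaving the between-group test unattached, because that is what the article states.

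**Conclusion.** The concern holds in limited form. The article gives the before-after values behind both primary endpoints to a within-patient test, confines the repeated-measures analysis to the same group, names an unadjusted between-group test without linking it to either endpoint, and uses no baseline covariate. A valid randomised analysis is compatible with the text but is not fixed by it.

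If the paired tests were read arm by arm, the chance of a misleading result in the intervention arm only would be about 1–25% at 20 per arm and 0–25% at 40 per arm. This rests on an assumed equal change of 0 to 1 SD of change in both arms. For LVMI at 20 per arm, ANCOVA raises power from 54% (follow-up only) to 58–93% over r = 0.3–0.8, against 41–90% for a change-score test. The correlation is an assumption, so these are ranges and not predictions. This is an improvement available at no cost, not proof that the planned trial cannot test its hypothesis.

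**What to change.** In the Statistical analysis section, state that the primary analysis of each primary endpoint is the difference between randomised arms at follow-up, estimated by ANCOVA (a linear model) with that endpoint's own baseline value as covariate and reported with a 95% confidence interval. For the oxygen-uptake endpoint, modelling either the follow-up value or the change with baseline as covariate gives the same treatment estimate, so the definition as a delta need not change. State that paired before-after comparisons within arms are descriptive only and will not support a claim of treatment effect.

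The cost is wording in the protocol or analysis plan, preferably settled before outcome data are examined by arm. Both visits are already scheduled in both arms, so no extra measurement or patient is needed.

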In conventional rehabilitation after stroke, the goal is to achieve maximum functional recovery [14, 15]. However, approximately 75% of individuals have associated heart disease after experiencing a stroke, thereby reducing their functional capacity to perform ADL [16–18]. Immobility after stroke results in resistance to physical exercise, including ADL [19, 20].

Several studies have reported that the maximum oxygen capacity (VO_2max_), defined as the critical (peak) oxygen capacity during aerobic activity, is reduced to 10–17 ml/kg/ min in the first 30 days after stroke, and does not reach values > 20 ml/kg/min after 6 months of the event [21–26]. VO_2max_ values after stroke decrease by 25–45% compared to healthy individuals in the same age group, which may interfere with the rehabilitation process and functional prognosis in the long term [27, 28].

Therefore, cardiorespiratory rehabilitation aims to provide greater functional independence during ADL with lower energy expenditure [28]. Several authors have reported that conventional rehabilitation is effective in improving the functional independence of individuals after stroke, but cardiorespiratory rehabilitation can restore aerobic capacity, reduce energy expenditure to perform ADL, and reduce the occurrence of cardiac events and recurrence of stroke [14, 15, 19, 20, 26–28]. However, the type, frequency, and appropriate method to achieve these goals during cardiorespiratory rehabilitation remain unclear in the literature. Hence, this study has clinical importance.

The main aim of this study is to evaluate the effect of a cardiovascular rehabilitation program on morphofunctional echocardiographic variables and functional capacity in patients with chronic ischemic stroke. In addition, we will assess the effects of cardiovascular rehabilitation on the inflammatory response, neurological status, nutritional status, cardiologic evaluation, and quality of life. We also aim to evaluate the association between clinical variables (age, anthropometric data, mean systolic blood pressure, 24-h diastolic blood pressure, magnitude of the nocturnal decrease in systolic blood pressure, diastolic and pulse pressure, use of antihypertensive medications) and echocardiographic variables and VO_2max_.

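### The aim of relating clinical variables to echocardiographic variables and VO2max is given a between-arm test and an undefined ANOVA/correlation procedure; a regression or correlation should be named (minor)

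*Protocol article*

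**What the plan says.** **The aim (Protocol article, Background, last paragraph).** "We also aim to evaluate the association between clinical variables (age, anthropometric data, mean systolic blood pressure", followed by ambulatory pressure measures and the size of the nocturnal fall, and ending "use of antihypertensive medications) and echocardiographic variables and VO_2max". Antihypertensive use is the only listed explanatory variable that is naturally categorical. The outcomes, echocardiographic measures and VO2max, are continuous.

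**The methods (Protocol article, Statistical analysis).** Three sentences bear on the aim:

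- The first opens with "The associations between clinical and echocardiographic variables will be evaluated by" and goes on to name Student's t-test when the data are normal. Its alternative is the "Mann-Whitney test with non-normal distribution for comparison between groups".
- The second gives change over time to a paired t-test.
- The third takes pairs of continuous measures within one arm, at both time points, and says that their associations "will be evaluated by means of repeated measures ANOVA correlation test".

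The section names no correlation coefficient and no regression model, and does not mention VO2max.

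**The concern.** The aim asks how one measured quantity varies with another across patients, for example whether indexed left ventricular mass is higher in patients with higher 24-hour pressure. A test between groups answers whether a variable differs between the control and intervention arms, the only groups that the protocol defines. A repeated measures ANOVA answers whether a mean changes over time. Neither output is a slope or a coefficient linking two continuous variables.

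An analyst who follows the text would produce p-values for arm or time differences and report them as associations. An analyst who departs from it would have to choose a method after seeing the data, over many pairs of variables, at p < 0.05. Either way the aim has no usable pre-specified analysis. This is a method stated wrongly in the document, not detail that an article may leave to an analysis plan.

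**Working it through.** The protocol gives no figure for this aim, so there is none to reproduce. The check compares question with method and then illustrates the result.

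**1. What each named test uses.**

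| Method | Data that enter | Question answered |
|---|---|---|
| t-test or Mann-Whitney between groups | outcome y and arm | Does y differ between arms? |
| Paired t-test | change in y | Does mean y change? |
| Repeated measures ANOVA, time effect | change in y | Does mean y change? |
| Repeated measures ANOVA, group-by-time | change in y and arm | Does the change in y differ between arms? |
| Correlation or regression | y and clinical variable x | How does y vary with x? |

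In the first four rows the clinical variable x does not enter the statistic, so its relation to y cannot affect the result. With two time points, the ANOVA time effect within one group is the paired t-test already listed separately.

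**2. Illustration by simulation.** Inputs: alpha 0.05, two-sided; 40 patients in total (Abstract) or 80 in total (40 per group, Sample size estimation), both shown because the document gives both; no arm effect and no time effect; 4000 runs per setting. The true correlation between x and y, or between their changes for the ANOVA rows, is an assumption. Rejection rates at correlation 0.5:

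| Test | N = 40 | N = 80 |
|---|---|---|
| Between-group t-test | 4.9% | 5.0% |
| ANOVA time effect | 5.1% | 4.8% |
| ANOVA group-by-time | 5.0% | 5.5% |
| Pearson correlation | 92% | 99.8% |

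At correlation 0.8 the first three rows stay between 4.6% and 5.8%, while Pearson rejects in every run. The simulated time effect used all N patients, not one arm. With no mean change the expected rate is 5% at either size.

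**3. Analytic check of the Pearson row.** Power ≈ Φ(atanh(ρ)·√(N − 3) − 1.960), with atanh(0.5) = 0.549.

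- N = 40: 0.549 × √37 = 3.34; 3.34 − 1.96 = 1.38; power ≈ 0.92.
- N = 80: 0.549 × √77 = 4.82; 4.82 − 1.96 = 2.86; power ≈ 0.998.

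Both agree with the simulation.

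**4. What the replacement could detect.** With alpha 0.05 and power 0.80, as in Sample size estimation ("with a fixed alpha error of 0.05 and beta error of 0.20, 37 patients per group will be needed"), the smallest detectable correlation is tanh((1.960 + 0.842)/√(N − 3)). This gives tanh(2.802/√37) = 0.43 for 40 pooled patients and tanh(2.802/√77) = 0.31 for 80. The protocol does not state sidedness; two-sided is assumed. That assumption reproduces the protocol's own sizes by the t-based method: 36.3 and 30.2, rounded up to 37 and 31 per group.

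**The case against.** **The t-test sentence may be a poor label for the arm comparison.** It ends by stating that purpose, and no other sentence in the section gives a between-arm test. This reading is plausible. It does not rescue the aim, because the clinical-echocardiographic associations then have no method except the undefined one.

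**The undefined term may mean a within-subject correlation for repeated measurements.** That would yield a coefficient, and the simulation does not cover it. This stands as a limit: a reader might infer that the named methods can estimate no association at all, and the text is too garbled to support that. But a within-subject correlation relates paired changes within patients. It cannot address age or other between-patient differences, which the aim includes, and the text says ANOVA.

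**A t-test can relate one listed variable to an outcome.** Antihypertensive use, coded yes or no, could be compared this way. That is true for this variable only, and the sentence ties the test to the group comparison.

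**A reader might take the loss from analysing each arm separately as the size of the error.** By the same formula the detectable correlation is 0.59 in one arm of 20 against 0.43 in 40 pooled. The arithmetic is right, but it measures the cost of splitting by arm, on one reading of the within-group wording. It does not measure the cost of using a test that ignores the clinical variable.

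**The aim is peripheral.** It is in neither the primary nor the secondary outcome list, and no sample size rests on it. This stands and sets the severity.

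**Conclusion.** The point holds as a mismatch between a stated aim and the methods stated for it. The between-group tests do not respond to an association between continuous variables. The other method is not a recognised procedure and, read as repeated measures ANOVA, does not respond either: rejection stays near 5% whether the true correlation is 0.5 or 0.8. VO2max is covered at most by the general reference to continuous variables.

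The simulated rates assume no arm or time effect. The qualitative conclusion does not rest on them, since it follows from what enters each statistic.

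Severity is minor. A reader might infer that the treatment comparison is compromised; the documents do not support that, because the primary between-arm comparison does not use these association analyses. The conflict between 40 patients in total and 40 per group is a separate matter.

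**What to change.** Replace both association sentences in Statistical analysis, for this aim, with wording to this effect:

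- **Baseline associations.** The echocardiographic variables and VO2max will each be related to each listed clinical variable by linear regression (or Pearson or Spearman correlation), using baseline values from all randomised patients with both arms pooled. The slope or coefficient will be reported with its 95% confidence interval. These analyses are exploratory. Pooling is natural here because baseline assessment precedes opening of the allocation envelope (Randomization and blinding).
- **Associations between changes, if wanted.** Restrict them to clinical variables that can change over 16 weeks, which excludes age. Adjust for the baseline value and randomised group. State that the group coefficient from such a model is not the treatment effect, because the model conditions on a change that occurs after randomisation.
- **Between-arm comparison.** Keep the t-test and Mann-Whitney wording for this purpose only, and drop the word associations from that sentence.

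The cost is a wording change while the trial is ongoing. It needs no new data or visits, and the planned software suffices.
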